**Methods/design:**

We will recruit 430 participants with IBS-D from approximately 30 primary and secondary care sites in England. Participants meeting the required abdominal pain and stool consistency criteria over a 2-week screening period will be randomly allocated to receive blinded treatment (Enterosgel® or placebo) for 8 weeks. This will be followed by an 8-week open-label treatment phase with Enterosgel®. Participants will be allowed to adjust their daily dosage during both phases based on their symptoms. Participants will then return to standard care and those who responded to treatment will receive a follow-up call 8 weeks later. Co-medication with loperamide will be permitted and use recorded. The primary outcome measure is the percentage of participants defined as responders for abdominal pain and stool consistency during at least 4 weeks in the 8-week blinded phase. Secondary outcome measures include stool frequency, stool consistency, abdominal pain, bloating, urgency, adequate relief, questionnaire scores and rescue medication use. Exploratory outcomes will be assessed in subsets of participants including qualitative and quantitative data on faecal microorganisms and biomarkers and gut-related measurements from magnetic resonance imaging data.

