### Recruitment

The study will be conducted at approximately 30 primary and secondary care sites and private gastrointestinal clinics in England. GP surgeries acting as patient identification centres will also refer patients to participating research sites. Sites will identify potential participants opportunistically and through searches of their patient databases, waiting lists, case records and referrals. Some research sites will utilise advanced software (Clinithink Ltd, UK) to identify potentially eligible patients from their clinical databases. The study can be advertised at participating sites and in public with materials approved by the Research Ethics Committee and the Health Research Authority. The study has developed a dedicated website which enables the public to check if they may be eligible and locate the contact details of their closest participating site. Finally, the study will recruit through the ContactME IBS registry [33], which contacts potentially eligible patients with details of the study. All potentially eligible patients will be provided with a patient information sheet either when visiting the GP/hospital/clinic or by post or email. Patients should be allowed at least 24 h to consider the study information before they are consented into the study.

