### Randomisation

Eligible participants will be randomised by a delegated member of the site research team to a double-blind treatment group (placebo or interventional) in a 1:1 ratio. Randomisation will be performed using a computer-based online randomisation tool (Sealed Envelope Ltd, UK). The randomisation algorithm is based on the minimisation method where treatment allocation is stratified by study centre.

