#### Planned analyses

Analyses will be conducted following intention-to-treat (ITT) principles with outcomes analysed according to the participant’s original, randomised group irrespective of deviations based on non-compliance. The statistician will remain blind to allocation until after the trial is complete and data locked.

All participant baseline data will be summarised descriptively by trial arm. Continuous measures will be reported as means and standard deviations while the categorical data will be reported as counts and percentages.

The primary outcome measure is the percentage of participants defined as study period responders. Where necessary, multiple imputation will be used to impute missing daily abdominal pain and stool consistency scores before the required derived variables are generated (see “Missing data” section below for further details). Once obtained, the primary outcome data will be summarised descriptively and logistic regression will be used to compare the placebo and Enterosgel® groups, with odds ratio and 95% confidence interval reported.

Secondary outcome data will be summarised descriptively at different time points by trial arm. The secondary outcomes will be analysed using either analysis of covariance (ANCOVA) models (for stool consistency and abdominal pain following multiple imputation), linear mixed effects models (continuous secondary outcomes), or mixed effects logistic regression models (binary secondary outcomes). The mixed effects models will contain indicator variables for treatment group and, where appropriate, time plus a time-treatment interaction. The models will be adjusted for the baseline measure of the outcome, where available.

Significance tests will be two-sided at the 5% significance levels unless otherwise stated. All models in the analysis of the double-blind and open-label phases will be adjusted for participant’s age and gender at baseline. Analyses will be undertaken in Stata v13 or later (to be confirmed in the final report).

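### The stated model covariates omit study centre, the only allocation factor named; if response differs between centres, the primary test is conservative and gives up some power

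*Protocol article*

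**What the plan says.** The Randomisation section of the protocol article sets a "double-blind treatment group (placebo or interventional) in a 1:1 ratio" and describes the method: "The randomisation algorithm is based on the minimisation method where treatment allocation is stratified by study centre". No other allocation factor is named. The Recruitment section gives the number and mix of centres: "The study will be conducted at approximately 30 primary and secondary care sites and private gastrointestinal clinics in England".

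Under Planned analyses, the primary comparison is described as follows: "logistic regression will be used to compare the placebo and Enterosgel® groups, with odds ratio and 95% confidence interval reported". Two covariate statements come later in that section. The first, in the paragraph on secondary outcomes, is "The models will be adjusted for the baseline measure of the outcome, where available". The second covers everything: "All models in the analysis of the double-blind and open-label phases will be adjusted for participant’s age and gender at baseline". For the mixed models the section adds "The mixed effects models will contain indicator variables for treatment group and, where appropriate, time plus a time-treatment interaction", without saying which random effects they contain. Stool consistency and abdominal pain as secondary outcomes are analysed by ANCOVA after multiple imputation.

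Centre is not named as a fixed effect, random effect or stratification variable in any of these analyses.

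**The concern.** Allocation and analysis do not match. The trial balances the arms within centre, but the covariates it commits to are age, gender and baseline outcome, none of which is an allocation factor.

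Balancing on a prognostic factor removes chance imbalance in that factor, so the true sampling variation of the treatment difference becomes smaller. A model without the factor still computes its standard error as if the imbalance could occur. The test then rejects too rarely under the null and gives up some power under the alternative.

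Centre could plausibly be prognostic here. The sites mix primary care, secondary care and private clinics, and the Discussion describes patients kept under secondary-care follow-up as often having more complex and refractory illness. At stake is the calibration and efficiency of the primary test. A positive result would not be put in doubt.

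**Working it through.** **1. The plan's own figure.** Inputs from Sample size estimation: 20% v 35% response, two-sided 5%, 90% power.

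n per group = (z₀.₉₇₅ + z₀.₉₀)² × [p₁(1−p₁) + p₂(1−p₂)] / (p₂−p₁)² = (1.960 + 1.282)² × (0.1600 + 0.2275) / 0.15² ≈ 181.

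The pooled-variance version gives 185. The stated 182 is within 1 and 3 of these, and its power recomputes to 89.7%. With 15% drop-out, 182/0.85 = 214.1, so 215 per group and 430 in total. The sample size reproduces and this point does not affect it.

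**2. Centre size.** 430/30 ≈ 14 enrolled and 364/30 ≈ 12 analysed per centre, on average.

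**3. Simulation of leaving centre out.**
- From the article: 2 × 182 = 364 analysed, 30 centres, 1:1 allocation, 20% v 35% under the alternative.
- Assumed: unequal centre sizes; allocation balanced within centre to about one participant; normal centre effects on the logit scale; a common rate of 27.5% under the null, the mean of 20% and 35%; overall arm rates held fixed at every ICC. Age and gender were not simulated.
- Centre SD: σ = √[ICC/(1−ICC) × π²/3]. For example, at ICC 0.10, σ = √(0.111 × 3.290) = 0.605; at ICC 0.20, σ = √(0.25 × 3.290) = 0.907.
- Compared: the Wald test from logistic regression without centre, and a Cochran-Mantel-Haenszel test stratified by centre. There were 6000 runs per setting.
- Monte Carlo error: √(0.05 × 0.95/6000) ≈ 0.3 points on type I error and √(0.9 × 0.1/6000) ≈ 0.4 points on power.

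The SE ratio is the mean model-based standard error of the log odds ratio without centre, divided by its actual standard deviation over the runs. A value above 1 means a conservative analysis.

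| Assumed ICC | SE ratio (null; 20% v 35%) | Type I error: no centre v stratified | Power: no centre v stratified |
|---|---|---|---|
| 0 | 0.99; 1.00 | 4.9% v 5.1% | 90.3% v 90.0% |
| 0.02 | 1.00; 1.02 | 4.9% v 5.0% | 90.4% v 90.6% |
| 0.05 | 1.02; 1.01 | 4.5% v 4.8% | 90.4% v 90.7% |
| 0.10 | 1.01; 1.02 | 4.6% v 5.4% | 90.8% v 91.8% |
| 0.20 | 1.07; 1.04 | 3.4% v 5.0% | 90.6% v 92.8% |

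**4. Reading.** The power given up is nil at ICC 0, 0.2 to 0.3 points at 0.02 to 0.05 (within Monte Carlo error), 1.0 point at 0.10 and 2.2 points at 0.20. Power without centre stays between 90.3% and 90.8% throughout, so the loss is power forgone and not a shortfall against the planned 90%.

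**The case against.** The strongest reply is that this is a condensed article that leaves detailed methodology to a statistical analysis plan not shown here, and nothing in it excludes centre. That would settle the matter if the article were silent on covariates. It is not silent: it fixes a set for all models of both treatment phases. An analysis plan that follows that set repeats the omission, and one that adds centre departs from what was published. The point stands as a stated choice that should be revisited.

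Other objections stand and limit the point:

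- A reader might infer that the models adjust for age and gender alone. The article also adjusts for baseline outcome where available.
- A reader might infer that centre is in no model at all. For the mixed models this would rest on silence, because their random effects are not described. The omission is clear only for the primary logistic regression and the ANCOVAs.
- A reader might conclude outright that the standard errors are too wide. That needs response to differ between centres, for which the article gives no figure. Some design features may keep differences modest: common entry thresholds, response defined against each participant's own baseline, and treatment shipped centrally.
- A reader might expect that adding centre must narrow the interval for the odds ratio. In logistic regression it also changes the estimand from one averaged over centres to one conditional on centre, and the conditional log odds ratio can have a larger standard error. The gain lies in the calibration and power of the test.
- The simulation used a stratified test as comparator, not a random-intercept model, and tight balance within centre. The article does not say whether the minimisation has a random element; looser balance would shrink the effect.

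**Conclusion.** The point holds in a limited form. The stated covariates leave out the only named allocation factor, most clearly in the primary logistic regression and the ANCOVAs. If centres differ in response, the primary test is conservative and gives up some power. The treatment comparison is not biased and type I error is not inflated, so the omission cannot by itself produce a false positive claim.

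The size depends on an assumed ICC. There is no effect at zero, standard errors are inflated by about 0 to 2% at 0.02 to 0.10, and by about 4 to 7% at 0.20, the top of the assumed range. The direction is secure given some between-centre variation; the magnitude is not known from the document. The case for changing the plan rests on the low cost of the change more than on the size of the loss.

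**What to change.** Add study centre to the primary logistic model and the ANCOVAs, and to the mixed models if it is not already there, as a random intercept or through a centre-stratified analysis. Keep age, gender and baseline outcome. Use fixed centre effects only with a pre-stated rule for pooling very small sites, since about 30 centres of 12 to 14 participants on average would leave many indicators sparse. State that the odds ratio is then conditional on centre. If the sponsor prefers to leave centre out, the plan should give the reason.

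The choice must be made before unblinding, so that the primary p-value is not open to challenge over which model was picked. The cost is a sentence or two in the analysis plan and no new data, because centre is already recorded for allocation. The downside is slightly more model complexity with many small centres, and no gain if centres do not differ.

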#### Missing data

Multiple imputation by chained equations will be used to impute missing values in daily abdominal pain and stool consistency scores before the primary outcome is derived. A sensitivity analysis will be undertaken to compare the results using multiple imputation with a complete case analysis. The complete case analysis will only use abdominal pain and stool consistency data where participants provided scores on all 7 days within a week (i.e. weeks containing at least one missing value of abdominal pain/stool consistency will be excluded).

### Quality assurance and control

The PI will be responsible for ensuring that the site is complying with the study protocol, current version of the World Medical Association Declaration of Helsinki, ICH-GCP guidelines and the applicable regulatory requirements. The PI will be responsible for ensuring that all site staff involved in the study have been appropriately trained and are qualified to conduct their delegated tasks. All medical staff involved in this study are required to have a certificate in GCP.

#### Data handling and record-keeping/archiving

All study-related paper documents (e.g. paper diaries, questionnaires, consent forms, study logs) will be filed in the study files during the study and archived at the site for 5 years after the end of the study.

#### Case report forms and source data

Data will be recorded in the eCRF from source documents defined in source data agreement with each site. All participants receive a unique study identification number (participant study ID) and no identifying data such as name, initials or date of birth will be collected in the eCRF. Source data will be available at the sites for monitoring and auditing purposes. Source data will include the original documents relating to the study, including demographics, eligibility checklists, informed consent forms and study questionnaires.

#### Record-keeping and archiving

All essential documents and trial data will be held by the sponsor for a minimum of 5 years after the end of the trial. Investigator site files should be archived at the participating sites for 5 years and should not be destroyed until authorisation to do so has been received from the sponsor.

#### Monitoring

Monitoring will be performed according to a risk-based, study-specific trial monitoring plan by monitors delegated by the sponsor. Monitoring includes checking participant eligibility criteria for all participants and confirming that data have been recorded correctly in the eCRF and any SAEs have been correctly reported and recorded.

#### Audits and inspections

All study documentation will be accessible to auditors and inspectors. All involved parties must keep the participant data strictly confidential. The Sponsor will conduct internal audits in accordance with a study audit plan.

#### Confidentiality and data protection

Access to source documents and other essential study documents will be permitted for purposes of audits and inspections. The study participants have consented to relevant sections of their medical notes and data collected during the study to be looked at by the research team, by individuals from Enteromed Ltd or contracted by Enteromed Ltd, from regulatory authorities or from the National Health Service (NHS) Trust, where it is relevant to this research. Participants have also consented to their name, home address and phone number being shared with Enteromed Ltd, and for Enteromed Ltd to provide this information to a study supplies warehouse and a courier company for the purposes of delivery of the study treatment. No identifiable data will be collected in the eCRF or will be published in any abstracts or publications resulting from the study.

#### Biological materials

Stool samples will be taken by the selected participants at home using a provided kit that includes a postage envelope for sending the sample to the central laboratory where the samples will be received within 6 days from collection and immediately stored at 4 °C upon arrival in the laboratory. Protein aliquots will be prepared within 24 h of receipt and stored at − 20 °C until testing within 3 days. All protein testing will be performed using standard enzyme-linked immunosorbent assay (ELISA) methodology. Nucleic acids will be isolated from samples within 1–2 business days after sample receipt and isolated nucleic acids will be immediately stored at − 80 °C until testing. Analysis reports will be uploaded by the laboratory onto a secure online portal accessible by the sponsor’s research team. Results will not be shared with the research sites or the study participants. The stool samples will be destroyed by the central laboratory after the samples have been analysed.

#### Safety assessments

Types of AEs associated with medical devices and applicable for this study are defined in accordance with the European Commission guidelines on medical devices [34]. AEs will be collected throughout the study from screening visit until week 24. The following information will be recorded for all AEs: medical term of the AE (SNOMED CT terminology), start date and date of resolution, seriousness, severity, study treatment action, outcome, relationship with the study treatment and expectedness. In case of a SAE related to study treatment(s) or procedures, the participant should be withdrawn from the study. Expectedness will be determined based on known side effects listed on the latest Instructions for Use for Enterosgel®. Currently listed known side effects of Enterosgel® are nausea and constipation.

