## Methods/design

### Study design

This will be a multi-centre, parallel arm, randomised, double-blind, placebo-controlled trial to evaluate the efficacy, tolerability and safety of a medical device, Enterosgel®, in the treatment of IBS-D in adults (Fig. 1). The study involves a 2-week screening phase, after which eligible participants are randomised to blinded treatment (Enterosgel® or placebo) for 8 weeks. Following the double-blind treatment phase, all participants will receive open-label Enterosgel® treatment for a further 8 weeks. At the end of the open-label treatment phase, all participants will return to standard care; however, those who responded to open-label treatment will receive a follow-up call 8 weeks later.

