#### Follow-up visit 2 (week 16)

Participants will complete study questionnaires (IBS-SSS, IBS-QOL, WPAI:IBS, PHQ-12 SS), and AEs and changes in medical history and medications will be reviewed. All participants will be asked the following question (replying (a) yes or (b) no): With regard to your IBS symptoms, compared with the way you felt before you started study treatment, have you, in the past 4 weeks, had adequate relief of your IBS symptoms? Those participants who respond yes will receive a follow-up phone call in 8 weeks. Those who respond no will receive no further follow-up from the research team and will complete the study at this visit.

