### Unblinding

Unblinding (code-break) should only be performed during the trial in a situation where information about the participant’s trial treatment is necessary in order to provide appropriate and optimal medical care. Requests for unblinding will first be reviewed by the principal investigator (PI) or sub-PI who evaluates the information and the importance of unblinding in the given circumstances. If they decide that unblinding is necessary to ensure appropriate medical care, an unblinding request form should be submitted through the eCRF system. Unblinded treatment allocation will then be sent to the person who requested the unblinding. In case of emergency unblinding, the PI will be responsible for deciding whether the participant should continue on trial treatment. Unblinded participants should be followed up according to the study protocol until the end of the study.

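### A related serious adverse event takes the participant out of the study, not only off treatment, so diary and later adverse event data that could be collected may be lost

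*Protocol article*

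**What the plan says.** The rule is in Safety assessments: "In case of a SAE related to study treatment(s) or procedures, the participant should be withdrawn from the study". It covers events related to treatment and events related to procedures, and its object is the study.

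The same section lists what is recorded for every adverse event, including "start date and date of resolution, seriousness, severity, study treatment action, outcome, relationship with the study treatment and expectedness". The action taken with treatment is therefore an item of its own, and the event's resolution and outcome are recorded. Adverse events are collected from screening to week 24.

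The primary outcome is the percentage of "responders for abdominal pain and stool consistency during at least 4 weeks in the 8-week blinded phase", derived from daily diary scores. Planned analyses sets an intention-to-treat comparison by randomised group regardless of non-compliance. Under Missing data, "Multiple imputation by chained equations will be used to impute missing values in daily abdominal pain and stool consistency scores" before the outcome is derived. The stated sensitivity analysis is a complete case analysis that drops any week with a missing score.

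After week 8, Study design says "all participants will receive open-label Enterosgel® treatment for a further 8 weeks". At week 16, only participants reporting adequate relief go on to the week 24 call. For the others: "Those who respond no will receive no further follow-up from the research team and will complete the study at this visit".

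**The concern.** Stopping treatment and leaving the study are different things. A participant harmed by the product or a procedure may have to stop it, yet may be quite willing to keep filling in a diary. The rule as worded does not use that willingness.

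Two kinds of information are at stake:

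- **Diary days in the blinded phase.** They go missing because of the event, so the reason for missingness is harm. Chained-equations imputation, as usually run, assumes data missing at random given what is in the model. The complete case analysis leaves the affected weeks out. Neither shows what the participant would have reported, and no later analysis can recover data that were never collected.
- **Later, separate adverse events.** They may go unrecorded up to week 16, or up to week 24 for someone who would have reported adequate relief, in the very people whose later safety course is of most interest.

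An analysis that follows everyone as randomised, whatever their compliance, is best served by keeping people under observation after they stop treatment.

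**Working it through.** **1. Inputs.** All are from the protocol article. Sample size estimation gives response rates of 20% (placebo) and 35% (active), 90% power, 5% significance, 182 per group, 15% drop-out and 430 in total. Randomisation gives a 1:1 ratio. Planned analyses gives two-sided tests and intention to treat. No related-SAE rate is given, so no case count is assumed and the effect is worked out per case.

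**2. The plan's own figure.** The unpooled normal formula is n = (1.960 + 1.282)² × (0.20×0.80 + 0.35×0.65) / 0.15² = 180.96, so 181 per group. The pooled version gives 185. The stated 182 lies between them. Inflating for drop-out, 182/0.85 = 214.1, so 215 per group and 430 in total. The sample size is not in dispute, and the fix does not change it.

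**3. When a case can affect the primary outcome.** The event must fall in the 8-week blinded phase, and responder status must still be open. With r response weeks among w completed weeks, and those weeks fully observed, status is open only if r < 4 and r + (8 − w) ≥ 4. A participant who already has four response weeks, or who can no longer reach four, contributes no error. Events in the open-label phase cannot alter the randomised comparison.

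**4. Largest shift per case.** This compares the result with the one from the diary data that continued follow-up would have given, using crude proportions and all 215 per arm.

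- Shift in one arm's responder rate: 1/215 = 0.00465, or 0.47 points in either direction.
- Share of the planned difference: 0.465/15 = 3.1%.
- Cases needed for a 1-point shift: 1/0.465 = 2.15, so at least 3 in one arm, all fully misclassified in the same direction.

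**5. On the odds ratio scale.** The planned value is (0.35/0.65)/(0.20/0.80) = 2.154. One fully misclassified case gives:

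| Arm of the case | Responder rate becomes | Odds ratio |
|---|---|---|
| Active, up | 0.3547 | 2.198 |
| Active, down | 0.3453 | 2.110 |
| Placebo, up | 0.2047 | 2.093 |
| Placebo, down | 0.1953 | 2.218 |

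The range for one case is therefore 2.09 to 2.22.

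**6. A typical rather than extreme case.** If a true non-responder in the active arm is imputed as a responder with probability 0.35, the expected overstatement is 0.35/215 = 0.16 points.

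**7. Scale.** The standard error of the log odds ratio at the planning rates is √[1/(215×0.35×0.65) + 1/(215×0.20×0.80)] = 0.223. The crude 95% interval is exp(0.767 ± 1.96×0.223), about 1.39 to 3.33. The plan also already allows for 0.15 × 430 = 64.5 drop-outs.

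**The case against.** The strongest reply is that the loss depends on text not shown. The article condenses a full protocol, and what is collected after withdrawal is commonly set out there. The article does not say in so many words that data collection stops. This stands as a limit on confidence. It does not remove the point, because the sentence criticised is a positive instruction, and a site following it as printed would end participation.

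It is also fair to say that the effect is negligible. A case must be serious, judged related, in the blinded phase, and still open as to response. The side effects listed for the product are nausea and constipation. This is conceded: there may be no cases, and one would be invisible beside the width of the confidence interval.

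Three stronger readings are tempting, and the documents do not support them.

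- *A reader might infer that follow-up of the serious event itself is cut short.* Resolution date and outcome are among the recorded items, and the section on reporting of serious adverse events sends every one to the regulator. Only later, separate events could be lost.
- *A reader might infer a contradiction with the Unblinding section*, which says "Unblinded participants should be followed up according to the study protocol until the end of the study" and "In case of emergency unblinding, the PI will be responsible for deciding whether the participant should continue on trial treatment". That follow-up is tied to the protocol, of which the withdrawal rule is part. The investigator's decision on treatment is the general rule for emergency unblinding, whereas the withdrawal rule is specific to related serious events. The two can be read together.
- *A reader might infer that intention to treat is breached.* It is not. Withdrawn participants stay in their randomised group and their missing scores are imputed.

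**Conclusion.** The point holds as a minor one. As worded, the rule ends observation where ending treatment would do, and it replaces diary days that could have been observed with imputed ones for a reason connected with harm. It may also lose later adverse events in the same participants.

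The effect on the primary result is at most 0.47 points in one arm per case, 3.1% of the planned difference, and may be zero. The figures rest on 215 analysed per arm, crude unadjusted proportions and the planning response rates. The bound takes each case as fully misclassified, so it is an upper limit and not an expectation. The conclusion also rests on reading withdrawal from the study in its ordinary sense. If the full protocol keeps collecting data after such withdrawal, only the wording needs attention. Confidence is medium for that reason.

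**What to change.** Reword the sentence in Safety assessments along these lines: after a serious adverse event related to study treatment or to a study procedure, study treatment is permanently discontinued, including open-label Enterosgel, and any procedure concerned is stopped. Diary, questionnaire, visit and adverse event collection continue as scheduled unless the participant withdraws consent.

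The open-label product should be named. A participant who stays in follow-up would otherwise reach the week 8 visit, where the design gives everyone Enterosgel. The treatment stop should apply to procedure-related events as well, so that the present protection is not loosened.

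The cost is one wording amendment and a little continued data collection in a few participants. The sample size and the analysis method are unchanged.
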